#### Statistical methods for ordinal outcomes with multiple measurements

For an ordinal outcome, such as the Ramsay score, cumulative link mixed model (CLMM) also known as proportional odds model was used. The response variable, Ramsay score, was modeled using the proportional odds assumption, where the cumulative log-odds of being at or below a certain category are modeled linearly in terms of predictors (see Additional file 3: Appendix C for model specification). The model estimates provided insights into how the probability of achieving a certain level of sedation changes over time and differs between treatment groups while controlling for other covariates.

#### Characteristics of the statistical tool and external packages

Analyses will be conducted using the R Statistical language (version 4.3.1; R Core Team, 2023) [28] on Windows 10 pro 64 bit (build 19,045), using the packages lme4 (version 1.1. [29]), Matrix (version 1.6.1.1; [30]), robustlmm (version 3.2.3; [31]), emmeans (version 1.8.9; [32]), ggeffects (version 1.3.2; [33]), sjPlot (version 2.8.15; [34]), performance (version 0.10.8; [35]), report (version 0.5.7; [36]) and gtsummary (version 1.7.2; [37]).

As our study is not a high-risk study that uses complex statistical methods, we decided to integrate a statistical analysis plan in this study protocol instead of publishing a separate, detailed statistical analysis plan before the analyses are undertaken [38, 39].

## Data collection and monitoring

Clinical data will be entered into protocols in paper form. After each assessment, the identifiers (e.g., name and birth date) will be anonymized, coded, and stored securely. The files will be backed up in a password-protected database. Data will be handled according to EU and local regulations.

### Interim analyses {21b}

No interim analyses are planned, and no serious adverse effects are expected to arise during the study, as all therapeutic methods are well-established in many other clinical settings.

### Methods for additional analyses (e.g., subgroup analyses) {20b}

As yet, there is no plan to perform subgroup statistical analysis.

### Methods in analysis to handle protocol non-adherence and any statistical methods to handle missing data {20c}

Analyses will be performed for the groups as randomized, primarily with an “as treated” approach. Participants withdrawing from the trial will be followed up, according to the routine clinical practices, but not analyzed further from the point of withdrawal unless they consent using the selected data.

In this type of clinical study, with a very short observation time of clinical data, which is monitored in the PACU, the possibility of missing values will be very low, especially in the primary outcome measure, as the data on oxycodone consumption will be collected using electronic PCA log. Overall, we expect missing outcome data to be minimal and only due to human error or equipment malfunction and, therefore, completely at random. In such a case, missing data will not be replaced.

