### Trial design {8}

The study is designed as a double-blind, randomized superiority trial. Equal, parallel 1:1 randomization will be performed using http://www.randomization.com (Dallal GE).

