### Criteria for discontinuing or modifying allocated interventions {11b}

Patients will be free to withdraw from the study at request at any time. Theoretically, in rare cases, it is possible that after randomization and receiving the placebo or intervention, the patient would be disqualified from the surgery or anesthesia due to some impossible-to-predict medical factors that would be revealed immediately before the scheduled operation or will not be able to complete the study treatment. In such a case, they would be withdrawn from the “as treated” analysis of the study outcomes.

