### Sample size {14}

The primary outcome of the study is 24-h oxycodone consumption. The mean 24-h oxycodone consumption in our previous study was 31.31 mg in patients on multimodal anesthesia [18] and SD was 13.7. In order to calculate sample size, we made the following assumptions: type 1 error (*α*) was set at 0.05; type 2 error (*β*) at 0.9 based on two-tailed testing. We considered a difference between groups (*δ*) greater than 10 mg, this being roughly 30% of the mean dose given above, and a standard maximal single dose of oxycodone in an adult patient, to be clinically significant. Using a sample size formula for two-tailed testing recommended in [27], a sample size of 76 should be enough to detect a substantial difference, as stated above. Taking into account an assumed mean drop-out of 15%, we have adopted a rounded-up sample size of 90 patients.

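### The plan makes an as-treated approach primary in a superiority trial and lets dosed patients be excluded on an undefined ground

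*Protocol article*

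**What the plan says.** The governing sentence is in the protocol article, section {20c}: "Analyses will be performed for the groups as randomized, primarily with an “as treated” approach". The as-treated label is used in one other place, section {11b}. That section, which describes such cases as theoretical and rare, states that "it is possible that after randomization and receiving the placebo or intervention, the patient would be disqualified from the surgery or anesthesia" because of unforeseen medical factors, "or will not be able to complete the study treatment". The consequence is: "In such a case, they would be withdrawn from the “as treated” analysis of the study outcomes".

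Section {20c} adds two rules. Patients who withdraw are "not analyzed further from the point of withdrawal unless they consent using the selected data". On missing values it says "Overall, we expect missing outcome data to be minimal and only due to human error or equipment malfunction", concludes that they are missing completely at random, and does not replace them.

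The design section {8} reads: "The study is designed as a double-blind, randomized superiority trial". The section on statistical software states that the analysis plan is integrated in this protocol rather than published separately. The wording in {20c} is therefore the operative rule. The article names no intention-to-treat or full analysis set, and no supporting as-randomised analysis.

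**The concern.** An as-randomised analysis classifies patients by allocation. An as-treated analysis classifies them by what they received. The sentence in {20c} joins the two and attaches the word for priority to the second. In a superiority trial the comparison by assigned arm should carry the conclusion, because only that comparison is protected by randomisation.

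The exclusion rule adds to the problem. The intervention is given once, before surgery. For a patient who has already received the capsule, being unable to complete study treatment is undefined. It could be read to cover someone lost after surgery because of sedation, a complication or stopped PCA. The protocol itself treats sedation as a dose-related effect of pregabalin ({6b}) and lists somnolence and dizziness among its commonest reactions ({22}). Exclusions of that kind could depend on both arm and opioid use, and so could bias the oxycodone difference in either direction.

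**Working it through.** **Step 1. The passages side by side.**

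| Question | Section {20c} | Section {11b} |
|---|---|---|
| How are groups formed? | By randomisation | Not stated |
| Which approach is primary? | As treated | Refers to the as-treated analysis only |
| Who is removed? | Withdrawals, from the point of withdrawal | Dosed patients not operated on; dosed patients unable to complete study treatment |
| What happens to incomplete totals? | Not replaced | Not stated |

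The reading that best reconciles the two is: compare the randomised groups, restricted to patients who were treated and operated on. That is a modified as-randomised or per-protocol set, depending on how the second exclusion ground is read. The text does not say which.

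**Step 2. The two exclusion grounds.** A patient who never has surgery has no 24-hour postoperative oxycodone total, so no analysis set can use that patient without inventing a value. The decision precedes surgery and is taken by blinded staff. The second ground has no such limit in time and no definition.

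**Step 3. Incomplete totals.** The primary outcome accumulates over 24 hours. A withdrawal part-way leaves a partial total. The missing-at-random statement is justified by recording error and equipment failure, and neither describes a withdrawal.

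**Step 4. What selective loss could do (illustration).** From the sample size section {14}: SD 13.7 mg, target difference 10 mg. Assumed: no true effect, normal data, and every loss drawn at random from the upper half of consumers in that arm.

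- Upper-half mean minus overall mean: 0.798 × 13.7 = 10.9 mg.
- Shift in the arm mean when a fraction f is lost: f × 10.9 / (1 − f).
- f = 15%: 0.15 × 10.9 / 0.85 = 1.93 mg. f = 5%: 0.05 × 10.9 / 0.95 = 0.58 mg.
- Losses of 0% and 15%: false difference 1.93 mg (19% of 10 mg). Losses of 5% and 15%: 1.93 − 0.58 = 1.35 mg (about 13%). Equal losses: none.

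A second illustration varies the strength of selection. Losses occur in the pregabalin arm only, and the lost patients have a mean k SDs above the arm mean. The bias is f × k × 13.7 / (1 − f). With 45 per arm randomised, the standard error is 13.7 × √(1/45 + 1/(45(1 − f))). Two-sided type I error comes from a z approximation with nominal level 5%.

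| f | k | Bias (mg) | Type I error |
|---|---|---|---|
| 5% | 0.5 | 0.36 | 5.2% |
| 5% | 1.0 | 0.72 | 5.7% |
| 10% | 0.5 | 0.76 | 5.8% |
| 10% | 1.0 | 1.52 | 8.1% |
| 15% | 0.5 | 1.21 | 6.9% |
| 15% | 1.0 | 2.42 | 12.6% |

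These are shifts in means. The planned primary test is a rank-sum test, so they indicate scale only.

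**Step 5. Power if everyone stays in the assigned arm.** The plan's drop-out step reproduces: 76 / 0.85 = 89.4, rounded up to 90. (The 76 itself does not follow from SD 13.7, 10 mg and 90% power, which give 40 per arm, 80 in total. That is a separate matter and does not affect this point.) With 45 per arm, power is Φ(10 / (13.7 × √(2/45)) − 1.96) = Φ(3.46 − 1.96) = 93.4%. For the rank-sum test, with an assumed relative efficiency of 0.955, it is about 92.3%. If an assumed 5% of the pregabalin arm had no benefit but stayed in its arm, z-test power would be 90.5%; at 10% it would be 86.9%, and at 15% 82.5%.

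**The case against.** The strongest defence is that the two sets will nearly coincide. There is one capsule, given in hospital and charted, so almost nobody can receive the other arm's treatment. Follow-up for the primary outcome is 24 hours, read from an electronic PCA log. The excluded cases are called rare, and those named first cannot supply an outcome. All of this stands, and it limits the likely size of the bias.

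Four stronger readings are tempting but not supported:

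- *That the plan names two rival primary analyses.* The word for priority attaches only to the as-treated approach; randomisation describes the groups. Nor does any section describe moving patients between arms.
- *That dropping dosed patients who are never operated on by itself gives up the protection of randomisation.* They have no outcome, and the set proposed under the fix omits them too. Blinding prevents exclusions driven by knowledge of the arm. It does not prevent those driven by drug effect, but the protocol describes unforeseen medical findings immediately before surgery.
- *That an "assumed mean drop-out of 15" per cent contradicts the expectation of few missing values.* The first is a planning allowance for drop-out. The second concerns recorded values, above all the PCA log. The 15% does not predict 13.5 missing totals among 90 patients.
- *That losses would mostly follow sedation, vomiting or complications.* No section says so, and such events do not erase a logged total.

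What the defence does not answer is the undefined second ground and the priority given to as-treated. Blinding is also not absolute: section {17b} permits unblinding for serious complications.

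**Conclusion.** The point holds as a defect in how the primary analysis set is fixed. An as-treated approach is made primary in a superiority trial, and one exclusion ground is open enough to admit postoperative removals related to treatment. Because the analysis plan is integrated in this document, the wording governs the trial's main conclusion and should be settled before unblinding.

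The practical bias is probably small. The figures of about 1.3 to 1.9 mg, and a type I error of up to about 12.6%, depend on assumed losses that differ between arms and relate to consumption. The documents support neither assumption. If the patients lost were low consumers, the direction would reverse.

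**What to change.** Reconcile sections {11b} and {20c} into a single definition:

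1. Primary set: all randomised patients who undergo sleeve gastrectomy and have postoperative PCA oxycodone data, analysed in the assigned arm regardless of later deviations.
2. Delete inability to complete study treatment as a ground for exclusion from the primary analysis.
3. Report every post-randomisation exclusion by arm and reason, including patients not operated on.
4. Keep an as-treated analysis, if wanted, as a sensitivity analysis only.
5. Replace the unconditional claim that data are missing completely at random with a simple sensitivity analysis for incomplete 24-hour totals, such as those from withdrawals who allow their data to be used. One option is to give incomplete totals the highest and then the lowest ranks. This item is secondary to the first four.

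The cost is a wording amendment and one or two extra analyses. No further patients or data are needed. Power with all 90 analysed by arm would be about 92% to 93% under the plan's SD and target difference.

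### Section {20c} gives two different rules for the primary analysis (as randomised and as treated), and {11b} removes dosed patients under an undefined clause, so protection by randomisation is not guaranteed

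*Protocol article*

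**What the plan says.** Section {20c} (protocol non-adherence and missing data) sets the analysis principle in one sentence: "Analyses will be performed for the groups as randomized, primarily with an “as treated” approach". On withdrawals, it says that these patients are followed up in routine care "but not analyzed further from the point of withdrawal unless they consent using the selected data". It expects missing outcome data to be minimal, to arise only from human error or equipment failure, and so to be completely at random: "In such a case, missing data will not be replaced".

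Section {11b} puts the as-treated rule to work and gives two triggers for removal. The first is that "after randomization and receiving the placebo or intervention, the patient would be disqualified from the surgery or anesthesia". The second is that the patient "will not be able to complete the study treatment". The consequence is the same for both: "they would be withdrawn from the “as treated” analysis of the study outcomes". The section describes such cases as theoretical and rare.

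Section {8} fixes the framework: "The study is designed as a double-blind, randomized superiority trial". Sections {11a} and {11c} describe the treatment as a single capsule, given once before surgery and charted. The section on statistical tools and packages says that the statistical analysis plan is integrated in this article.

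**The concern.** An as-randomised analysis keeps every patient in the assigned arm, whatever happens later. An as-treated analysis lets events after randomisation decide who is counted, and where. Under the sentence in {20c}, two statisticians could build two different primary datasets and both claim to follow the plan. The word 'primarily' favours the less protected one.

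Section {11b} makes this more than loose wording. Once a single capsule has been swallowed, it is unclear what remains to be completed, so the second trigger has no defined content. Whoever applies it must decide what it covers, and the reason for a removal could be related to the drug or to the outcome. In a superiority trial the inference rests on comparing the groups that randomisation formed. If removals are related to oxycodone need and differ between arms, both the type I error and the estimated difference in mg are affected.

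**Working it through.** **The statements side by side**

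| Question | As randomised ({20c}, first half) | As treated ({20c}, second half, with {11b}) |
|---|---|---|
| Which arm? | Assigned arm | Not stated; {11b} only removes patients, it does not move them |
| Surgery cancelled after the capsule? | Would count as randomised, but has no postoperative outcome | Removed |
| Treatment not completed? | Stays in | Removed; term undefined |

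The two columns differ on the last row in a way that changes the primary dataset. The article names no intention-to-treat or modified intention-to-treat set, and no sensitivity analysis on all randomised patients.

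**How many patients could be lost**

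Section {14} plans 76 evaluable patients and a 15% drop-out. 76 / (1 − 0.15) = 89.4, rounded up to 90, so this step reproduces. The allowance is 90 − 76 = 14 patients, or 7 of 45 per arm. It covers drop-out of every kind and does not forecast removals under {11b}.

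**What selective loss would do**

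Inputs from the article: mean 31.31 mg, SD 13.7 mg and difference 10 mg (section {14}); Wilcoxon rank-sum test and two-sided alpha 0.05 (sections {20a} and {14}). Assumptions not in the article: normal outcome, 45 per arm, and each patient's odds of removal multiplied by e for every SD of higher consumption. Simulation with 20,000 runs and no true effect (simulation error about ±0.3 percentage points):

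| Removed | Type I error | False difference |
|---|---|---|
| None | 5.2% | 0.0 mg |
| 1 of 45, one arm | 4.7% | 0.3 mg |
| 2 of 45, one arm | 5.5% | 0.6 mg |
| 3 of 45, one arm | 6.0% | 0.9 mg |
| 7 of 45, one arm | 10.4% | 2.0 mg |
| 7 of 45, both arms by the same mechanism | 5.9% | 0.0 mg |

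Repeat runs of the 7-of-45 one-arm case lie between 10.3% and 10.9%, with 2.05 to 2.1 mg. That is about 21% of the 10 mg target (2.1 / 10). Removal at random leaves the type I error near 5%. An extreme bound, in which the 7 removed from one arm are exactly its heaviest users and the other arm loses 7 at random, gives about 22% and 3.7 mg. Nothing in the article makes that pattern likely.

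**Power in the opposite direction**

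Suppose the placebo arm loses 7 of 45 selectively when the true effect is 10 mg. The observed difference shrinks to about 7.95 mg.

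- Standard error = 13.7 × √(1/45 + 1/38) = 3.02 mg.
- Power at 10 mg: Φ(10/3.02 − 1.96) = Φ(1.35) = 91.2%.
- Power at 7.95 mg: Φ(7.95/3.02 − 1.96) = Φ(0.67) = 75.0%.

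**The case against.** The strongest reply is that the authors have only chosen a poor label. Arms are compared as assigned, {11b} shows that 'as treated' means dropping some patients, and nothing regroups patients by the capsule received. Receiving the other arm's capsule should be rare with one identical-looking, pharmacy-made, charted capsule. This stands: the plan looks most like a mislabelled per-protocol or modified intention-to-treat set.

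The first trigger in {11b} is also defensible. A patient whose operation is cancelled has no postoperative oxycodone total, and the fix below leaves such patients out too.

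Blinding of patients, staff and assessors ({17a}), with the sequence withheld from the principal investigator until the last patient has finished ({16c}), prevents deliberate selection by arm. It does not prevent loss caused by an effect of the drug itself.

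A reader might infer that the second trigger removes patients for a stopped PCA pump, a protocol deviation or high opioid need. The article does not say so. A capsule not taken or not retained would fit the clause equally well. The sound criticism is that the clause is undefined.

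The 7-of-45 case can fairly be called pessimistic. It spends the whole drop-out allowance on selective loss in one arm, while {11b} speaks of rare cases and {20c} expects minimal missing data.

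What the reply does not remove is that one sentence states two rules, and that a post-randomisation exclusion without a definition feeds the primary analysis. A separate analysis plan cannot be assumed to settle this, because the article says that the plan is integrated in it.

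**Conclusion.** The point holds as a defect in a stated rule. The primary analysis set is contradictory, and the approach named as primary is the less protected one for a superiority trial. Protection by randomisation is therefore not guaranteed. A reader might go further and conclude that the comparison is biased or that randomisation is lost. The article does not support that, because no selective removal has been shown and few removals are expected.

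If few patients are removed, as the article expects, the effect is small: type I error near 5 to 6% and 0.3 to 0.9 mg for 1 to 3 of 45 lost from one arm. It reaches about 10 to 11% and about 2.1 mg only if 7 of 45 are lost selectively from one arm. It is about zero in bias if both arms lose patients alike. All of these figures rest on the assumed link between consumption and removal, for which the article gives no data.

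The rules on withdrawals and missing data belong to the same problem. Missing completely at random is argued only for human error and equipment failure. That argument does not cover withdrawals or removals under {11b}.

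**What to change.** 1. In {20c}, replace the sentence on the analysis principle with: *The primary analysis includes all randomised patients who undergo LSG, analysed in the assigned arm whatever capsule was taken. An as-treated analysis is a labelled sensitivity analysis.*
2. In {11b}, delete inability to complete the study treatment as a reason for removal from the primary analysis. Leave out only patients whose surgery did not take place. Decide this before unblinding, and list these patients by arm and reason.
3. In {20c}, state that oxycodone data recorded up to withdrawal are used where consent allows. Report withdrawals and missing 24 h totals by arm, with a simple sensitivity analysis for the missing totals (for example, giving them the highest and then the lowest ranks).

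The cost is a small amendment, which under {25} goes through ethics review and a registry update, and one or two extra analyses. No extra patients or data are needed. The article reports that recruitment is under way, so the change should be made and dated before the allocation sequence is released.

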### Plans to give access to the full protocol, participant-level data and statistical code {31c}

Data associated with published work will be available upon reasonable request. Should this occur, only anonymous data will be made available to protect participant confidentiality.

### Composition of the coordinating center and trial steering committee {5d}

The study will be coordinated by the principal investigator and one dedicated researcher, who will coordinate all phases, including randomization and data storage.

### Composition of the data monitoring committee, its role and reporting structure {21a}

The study includes no interim analysis; the patients involved have non-critical conditions and will undergo treatment for a relatively brief period. Furthermore, pregabalin has a well-established safety profile with a very low probability of harm to the patient. Therefore, apart from the supervision of the Medical University of Warsaw, no external data monitoring is planned.

### Adverse event reporting and harms {22}

Most reported adverse effects caused by pregabalin were mild to moderate intensity, dose-dependent, and occurred within the first 2 weeks of initiating treatment. The most common adverse reactions reported across all patient populations in premarketing controlled trials, which occurred in greater than or equal to 5% of patients taking pregabalin and twice the rate reported by patients receiving placebo, were: somnolence, dizziness, blurred vision, difficulty with concentration/attention, dry mouth, edema, and weight gain [40].

In our trial, participants will be advised to contact ward personnel as soon as possible in case of unexpected or adverse effects or any discomfort supposedly associated with the capsule intake. All the patients will be supervised during their hospital stay, and all possible adverse events or reactions will be observed, recorded, and reported in the study.

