The 2018 ESRA procedure-specific postoperative pain management (PROSPECT) recommendations suggest the use of pregabalin in patients who cannot receive simple analgesics [7]. The above statement is based on two trials involving pregabalin perioperatively in patients who underwent LSG. In the study by Schulmeyer et al., a single 150 mg dose of pregabalin 2 h before surgery allowed for a decrease in the total dose of opioids administered in the postoperative period by 50%. What is essential, pregabalin did not increase the rate of experienced side effects such as excessive sedation or dizziness [8]. Nonetheless, this study has significant limitations, as the study did not implement Patient-Controlled Analgesia (PCA) and more importantly, the authors of the PROSPECT recommendations underline the lack of multimodal analgesia in both the study and control groups. In a study performed by Salama et al. [9], a 68% decrease in the total dose of opioids was possible with 75 mg of pregabalin and a dexmedetomidine infusion of 0.4 μg/kg/h. However, in this study, it is impossible to distinguish between the effects of both medications, as dexmedetomidine has also been proven to have analgesic potential. Similar difficulty in assessing the isolated pregabalin effect has been reported in the observational study by Lam et al. In their study, pregabalin, 150 or 300 mg, depending on the patient's weight, was given as an element of multimodal analgesia to reduce or eliminate total postoperative opioid use [10]. In another trial concerning pregabalin, Alimian et al. demonstrated a reduced incidence of PONV with concomitant lower pain scores throughout the postoperative period in patients undergoing laparoscopic gastric bypass surgery [11]. The limitations of this study include a lack of assessment of sedation and the effects of specific components of multimodal analgesia, which can vary depending on the procedure and may differ between types of surgeries; thus, they are not fully generalizable to patients undergoing LSG [12].

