### Outcomes {12}

The primary outcome measure will be total oxycodone consumption 24 h after surgery. Secondary outcome measures will be as follows: pain scores on the NRS scale at 1, 6, 12, and 24 h after surgery, postoperative sedation on the Ramsay scale [25], PONV impact scale [26], the incidence of desaturation episodes < 94% and episodes of blurred vision at 1, 6, 12 and 24 h after surgery, intraoperative heart rate (HR), systolic blood pressure (SBP), diastolic blood pressure (DBP), mean blood pressure (MBP): their highest and lowest values, time of MAP < 65 mmHg, > 90 mmHg, HR < 50 and > 90, total fluid volume, total ephedrine dose and patient's comfort assessed in QoR-40 [22] questionnaire at discharge.

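### Dizziness, which the protocol names as a common pregabalin reaction, has no scheduled assessment or planned analysis, so its absolute frequency may be understated

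*Protocol article*

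**What the plan says.** Adverse event reporting and harms {22} describes the most common reactions in premarketing trials as those that "occurred in greater than or equal to 5% of patients taking pregabalin and twice the rate reported by patients receiving placebo", and says that these "were: somnolence, dizziness, blurred vision, difficulty with concentration/attention, dry mouth, edema, and weight gain". Dizziness is second on the list.

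Two of the first three reactions are followed on a schedule. Outcomes {12} includes "postoperative sedation on the Ramsay scale", which covers somnolence, and "the incidence of desaturation episodes < 94% and episodes of blurred vision at 1, 6, 12 and 24 h after surgery". Table 1 gives both a row with marks at 1, 6, 12 and 24 h. The statistical section plans a mixed logit model for blurred vision and a cumulative link mixed model for the Ramsay score.

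Dizziness has no entry in Outcomes {12}, no row in Table 1 and no planned model. Background and rationale {6a} nevertheless reports of the earlier single-dose 150 mg study that "pregabalin did not increase the rate of experienced side effects such as excessive sedation or dizziness".

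The general route for harms in {22} has two parts. First, "participants will be advised to contact ward personnel as soon as possible in case of unexpected or adverse effects", or in case of "any discomfort supposedly associated with the capsule intake". Second, patients are supervised during the stay, and "all possible adverse events or reactions will be observed, recorded, and reported in the study".

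**The concern.** The abstract states that the trial will explore the efficacy and safety of 150 mg pregabalin and may support a reassessment of recommendations. Dizziness is prominent in the protocol's own list of expected reactions and in its account of the earlier study at the same dose. It is nevertheless collected by a less systematic method than blurred vision, which stands next to it on the list.

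Staff cannot reliably observe a subjective symptom unless they ask about it, and the article states no question, checklist or time point for doing so. A low count could then reflect how the symptom was collected as much as how often it occurred, and it would not be comparable with the count for blurred vision. At stake are the absolute frequency of dizziness and the absolute difference between arms. The primary outcome is not affected.

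**Working it through.** The plan gives no dizziness figure to reproduce. The check is a comparison of sections, followed by an illustration under assumed values.

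**Comparison of sections**

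| Reaction named in {22} | Outcomes {12} | Table 1 | Planned model |
|---|---|---|---|
| Somnolence (as Ramsay sedation) | yes | 1, 6, 12, 24 h | cumulative link mixed model |
| Dizziness | no | no | none |
| Blurred vision | yes | 1, 6, 12, 24 h | mixed logit model |

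QoR-40 does not fill the gap, whatever its items cover. It is completed once at discharge and analysed as a single score by a rank-sum test.

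**Illustration**

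From Sample size {14} and Trial design {8}: 90 patients allocated 1:1, so 90 / 2 = 45 per arm.

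Assumed, because the documents give neither: true rates p1 (pregabalin) and p0 (placebo), and a share s of cases captured, equal in both arms. A twofold ratio is used, in line with the criterion in {22}.

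- Expected recorded cases: 45 × p × s in each arm.
- Recorded risk difference: s × (p1 − p0), so it shrinks by the factor s.
- Ratio of recorded rates: (s × p1) / (s × p0) = p1 / p0, so it does not change.

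| Assumed true rates | s | Expected cases | Risk difference | Power, normal approx. / Fisher |
|---|---|---|---|---|
| 20% vs 10% | 1 | 9.0 vs 4.5 | 10 points | 26% / 18% |
| 20% vs 10% | 0.5 | 4.5 vs 2.25 | 5 points | 14% / 6% |
| 20% vs 10% | 0.25 | 2.25 vs 1.1 | 2.5 points | 9% / 1% |
| 10% vs 5% | 1 | 4.5 vs 2.25 | 5 points | 14% / 6% |
| 10% vs 5% | 0.5 | 2.25 vs 1.1 | 2.5 points | 9% / 1% |
| 40% vs 20% | 1 | 18 vs 9 | 20 points | 55% / 46% |
| 40% vs 20% | 0.5 | 9 vs 4.5 | 10 points | 26% / 18% |

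Power is for a two-sided test at 0.05.

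**Precision with full capture, 20% vs 10%**

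Half-width of the 95% CI = 1.96 × √[(0.20 × 0.80 + 0.10 × 0.90) / n] = 1.96 × √(0.25 / n).

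- n = 45 per arm: 1.96 × 0.0745 = 0.146, about ±15 points.
- n = 38 per arm (76 / 2, the plan's number before drop-out is added): 1.96 × 0.0811 = 0.159, about ±16 points.

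Under-capture therefore lowers the reported frequency and the absolute excess, but a formal comparison would be weak even with complete capture.

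**The case against.** The strongest reply is that {22} already promises supervision and the recording of all events, so dizziness is not lost. That stands in part. A reader might infer that dizziness is recorded only if the patient volunteers it, but the text does not support this because staff observation is a second route. The postoperative form is also not shown, and Plans for assessment and collection of outcomes {18a} describes its content by example only, so a prompt on the form cannot be ruled out. The article does show that dizziness is not a scheduled outcome and that no prompt is stated.

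A reader might also infer that patients must link a symptom to the capsule before reporting it. The capsule wording qualifies only discomfort; unexpected or adverse effects need no such link. How patients would attribute dizziness after anaesthesia and on oxycodone is conjecture.

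It is tempting to say that the trial will understate dizziness, or that its comparison of arms will be biased. Neither is established. The rates and capture shares above are assumptions. The list in {22} pools all patient populations in premarketing trials and includes weight gain, so it is not a single-dose perioperative profile. With blinding, under-capture should be similar in both arms and the expected risk ratio unchanged.

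Nor could scheduled collection let the trial confirm or refute the earlier dizziness result, given an interval of about ±15 points. The rationale mentions dizziness there as an example of a side effect, and its stated criticisms of that study concern other matters.

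Finally, concentration difficulty and dry mouth are on the same list and equally unscheduled. That is fair. Dizziness is singled out because the rationale itself cites it.

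**Conclusion.** The concern holds as a minor point, with moderate confidence. The protocol treats dizziness as a common reaction and as a relevant earlier safety result, yet schedules no assessment and plans no analysis of it, while its neighbours on the list have both. The unprompted route may understate the absolute frequency and the risk difference. If capture were 25% to 50% in both arms, each would shrink to 25% to 50% of its true value: a true 10-point difference would be recorded as 2.5 to 5 points.

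These sizes are illustrations under assumed rates and capture shares, not estimates for this trial. The conclusion also assumes that the postoperative form carries no dizziness prompt beyond what the article describes. If it does, only the outcome list, Table 1 and the reporting plan need to change.

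**What to change.** From a stated calendar date, add dizziness (yes/no) to Outcomes {12}, Table 1 and the postoperative form at 1, 6, 12 and 24 h. Use the same fixed question in every patient, worded to cover the interval since the previous assessment.

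Report, per arm, the patients with any dizziness over 24 h among those randomised after that date, with a risk difference and 95% CI. Label this a descriptive safety estimate, not a powered test. Restricting it to patients randomised after the date keeps the comparison randomised. State that dizziness in earlier patients was collected non-systematically.

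Reword {22} so that symptoms are recorded whether or not the patient links them to the capsule.

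The cost is a minor amendment through the route in {25} and one extra item at four assessments that are already made. Patients already enrolled will lack the item. The estimate will be imprecise, at about ±15 points under the 20% vs 10% assumption with 45 per arm, and wider because fewer will have been asked.
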